## Abstract

**Introduction:**

This project applies a Learning Healthcare System (LHS) approach to antibiotic prescribing for common infections in primary care. The approach involves iterations of data analysis, feedback to clinicians and implementation of quality improvement activities by the clinicians. The main research question is, can a knowledge support system (KSS) intervention within an LHS implementation improve antibiotic prescribing without increasing the risk of complications?

**Methods and analysis:**

A pragmatic cluster randomised controlled trial will be conducted, with randomisation of at least 112 general practices in North-West England. General practices participating in the trial will be randomised to the following interventions: periodic practice-level and individual prescriber feedback using dashboards; or the same dashboards plus a KSS. Data from large databases of healthcare records are used to characterise heterogeneity in antibiotic uses, and to calculate risk scores for clinical outcomes and for the effectiveness of different treatment strategies. The results provide the baseline content for the dashboards and KSS. The KSS comprises a display within the electronic health record used during the consultation; the prescriber (general practitioner or allied health professional) will answer standard questions about the patient’s presentation and will then be presented with information (eg, patient’s risk of complications from the infection) to guide decision making. The KSS can generate information sheets for patients, conveyed by the clinicians during consultations. The primary outcome is the practice-level rate of antibiotic prescribing (per 1000 patients) with secondary safety outcomes. The data from practices participating in the trial and the dashboard infrastructure will be held within regional shared care record systems of the National Health Service in the UK.

**Ethics and dissemination:**

Approved by National Health Service Ethics Committee IRAS 290050. The research results will be published in peer-reviewed journals and also disseminated to participating clinical staff and policy and guideline developers.

**Trial registration number:**

ISRCTN16230629.

STRENGTHS AND LIMITATIONS OF THIS STUDYThis protocol describes a pragmatic cluster randomised controlled trial with randomisation of general practices to periodic practice-level and individual prescriber feedback using dashboards only compared with dashboards plus a knowledge support system (KSS) that can be activated during consultations.These interventions will be applied to antibiotic prescribing for common infections in primary care, an important area for clinical improvement given rising antimicrobial resistance.The design of the KSS was informed by two mixed-methods codesign workshops in which clinicians identified: key information to extract from care records (such as antibiotic prescribing history); recommended actions; personalised treatments; risk indicators and content for patient information sheets.The primary research question is what is the effect on antibiotic prescribing of the KSS intervention within a learning health system implementation?A pilot phase will be initially conducted, with the recruitment target of 20 practices across two regions to examine feasibility and acceptability.

## Introduction

Translating research findings into routine clinical practice is a major challenge. The Learning Healthcare System (LHS) approach has been proposed to better integrate research into clinical practice.^1^ It involves iterations of data analysis (data to knowledge), feedback to clinicians (knowledge to performance) and implementation of quality improvement activities by clinicians (performance to data).^2 3^ In the LHS, feedback can either be provided periodically through for example online dashboards or during consultations with patients using a knowledge support System (KSS). We use the term KSS as distinct from a Clinical Decision Support System because the information provided is about the condition, common complications and treatment options in general rather than specific decisions. Activation of KSS linked to electronic health records (EHRs) has been proposed for augmenting clinicians’ knowledge during consultations with patients.^4^ An icon on the clinicians’ computer screen provides access to information on ‘patients like mine’ (eg, the risk of developing clinical complications in similar patients), recommendations (eg, best not prescribe amoxicillin given this patient’s frequent prior use) and a patient information sheet tailored to their condition and treatment. The information on similar patients could be drawn from several sources such as historic data on clinical outcomes from comparable patient groups.^4^ Thus, the KSS provides contextual information where a Clinical Decision Support System would point to a desired decision.^5^

In this project, the LHS approach will be applied to antibiotic prescribing for common infections in primary care. Primary care accounts for 72% of antibiotic prescribing in England.^6^ Overuse of antibiotics is a major public health concern as it increases antimicrobial resistance. The National Health Service (NHS) 2019 Long Term Plan pledged action to optimise antibiotic uses, reducing inappropriate prescribing. The LHS approach will also include personalised patient information sheets that the clinician can provide to patients during consultation after KSS activation. A recent Cochrane review found that people exposed to decision aids feel more knowledgeable, better informed and clearer about their values. It also found improved knowledge and accurate risk perceptions when decision aids are used within the consultation.^7^

### Research questions

The research question is whether a KSS intervention within an LHS implementation can improve antibiotic prescribing without increasing the risk of complications? Practices that have implemented the KSS will be compared with practices that have not (ie, randomised cluster trial). The LHS approach will involve detailed data analysis followed by feedback to clinicians.

## Methods and analysis

### Prior development of study interventions

#### Periodic feedback

A previous project piloted and implemented the IT infrastructure for the LHS (ie, data analytics, feedback to clinicians) on antibiotic prescribing care in UK primary care. This project (BRIT: Building Rapid Interventions to reduce AMR and over-prescribing of antibiotics) was part of the £20 million Department of Health and Social Care funded Connected Health Cities programme (https://www.connectedhealthcities.org/). This initial BRIT project developed practice-level feedback on antibiotic together with feedback on individual prescribers.^8^ These dashboards comprise a variety of antibiotic prescribing measures that were developed with clinical stakeholders.^9^ They currently provide information at practice level on the drivers of antibiotic prescribing (overall and by indication), analyses of prescribing of inappropriate types of antibiotics (deviating from guideline) and extent of risk-based prescribing. Importantly, the dashboards will allow clinicians to review data at different levels, including for example prescribing rates of a specific antibiotic to the individual patients prescribed that antibiotic, and comparison to other practices in the region.^9^

#### KSS during consultation

Our KSS intervention was developed based on the results of two mixed-methods codesign workshops to gauge the acceptability of a prototype.^10^ Clinicians identified the following key requirements: ease and efficiency of use, integration of systems, patient-centeredness, personalisation and training. The KSS needs to include extraction of pertinent information from the care record (such as antibiotic prescribing history), recommended actions, personalised treatment, risk indicators and electronic patient information leaflets. The anticipated acceptability and intention to use the KSS, was moderate to high. While time was identified as a cost/burden, this was outweighed if the KSS improved patient outcomes and increased prescribing confidence. All the main requested features were implemented in the KSS except personalised treatment recommendations because current treatment guidelines do not cover all of the frequently encountered clinical challenges, such as frequent repeat antibiotic prescribing shortly after the first one.

### Study design, participating sites and overview of interventions

The study will be a pragmatic cluster randomised controlled trial with 1:1 randomisation of practices to:

Periodic feedback to general practices using practice-level+individual prescriber feedback dashboards. Online supplemental appendix 1 provides examples of different dashboards.orPractice-level+individual prescriber feedback dashboards+KSS during consultation with the clinician providing content (such as an information sheet) that is personalised to the patient.

10.1136/bmjopen-2023-076296.supp1Supplementary data

The study sites will include general practices located in the North-West of England that provide patient-level data to a regional shared care record system (https://www.graphnethealth.com), which is deployed in Greater Manchester, Wirral and Cheshire/Merseyside regions, together covering a 5.4 million general population. The shared care record collates data from various NHS organisations to support direct patient care, service planning and research. Researchers access anonymised patient-level data through a secure data analytic environment linked to the shared care records.

### Details of study interventions

#### Content of KSS for clinicians

Figure 1 shows the architecture of the KSS including data extracted from the patient’s EHR, ability for clinicians to enter details on infection severity, estimation and presentation of risk scores, generation of personalised patient leaflet and write-back of codes to the EHR. The KSS will be available for all clinicians in the practices randomised into the KSS arm of the study. Eight screens are accessible within the KSS. Figure 2 shows screen 1 of the KSS after activation (and online supplemental appendix 2 shows additional examples of KSS screenshots). This provides for the selection of the type of common infection and indicators of problem significance and duration. Screen 2 is the symptom survey which provides a survey with list of symptoms to capture infection severity. An example is the Feverpain score for acute sore throat, including questions such as fever in past 24 hours, presence of cough or coryza and physical examination findings.^11^ Screen 3 (patient summary) includes an extraction of relevant information as recorded in the patient’s EHR: the data on recent antibiotic prescribing (dates and types) and information on presence of allergies. This screen is populated automatically after KSS activation. Screen 4 (patient risks) gives personalised information including risks of:

10.1136/bmjopen-2023-076296.supp2Supplementary data

Developing infection-related complications that lead to hospital admission.Resistance based on number of prior antibiotics prescribed to the patient in the previous 12 months.Antibiotic failure indicating probability may be prescribed another antibiotic within 30 daysSevere adverse outcomes such as hospital admission for renal failure.

**Figure 1 F1:**
[figure not shown]
Architecture of the knowledge support system.

**Figure 2 F2:**
[figure not shown]
Example of a KSS screen after activation within the care record system during consultation highlighting the patient’s details (fictional) with the active record and the various screen available to the clinician. KSS, knowledge support system.

These personalised risk scores are based on risk prediction models including characteristics such as age, gender, clinical and medication risk factors, ethnicity and socioeconomic status. These risk prediction models were developed and tested in the OpenSAFELY platform (https://opensafely.org) or the Clinical Practice Research Datalink GOLD and Aurum (https://cprd.com/).^12 13^ Risks are calculated using these algorithms which are combined with the patient’s specific characteristics as recorded in the EHR. The clinician is given links to the relevant National Institute for Health and Care Excellence (NICE) guideline for the infection in screen 5 (treatment guidelines). The clinician can then consider these risk scores alongside other information when considering whether to prescribe an antibiotic, line up a back-up antibiotic or discuss with the patient alternative care pathways without antibiotics (treatment decision is recorded in screen 6). Once the shared decision-making process is complete, the clinician may provide an information sheet for the patient, particularly where an antibiotic is not being prescribed to advise the patient of the decision and provide the personalised risk scores (screen 7 with patient leaflet). Screen 8 allows the clinician to initiate a write-back function which will write back to the care record the diagnosis, symptoms and treatment as SNOMED codes. The KSS has been developed for use with EMIS which is the most common primary care record system in England.^14^ Patient records remain confidential, and all data flows happen within the NHS.

#### KSS content for patients

We developed personalised patient information sheets that show tailored risk/benefit information based on patient-specific estimates of for example the risk of being admitted to hospital for infection-related complications. These information sheets are populated by the results of the KSS activation. The clinician can provide these to patients after consultation, in addition to any existing generic patient information sheets (TARGET) which also include information on illness duration, self-care advice, prevention advice and advice on when to re-consult (https://www.rcgp.org.uk/clinical-and-research/resources/toolkits/amr/target-antibiotics-toolkit/leaflets-to-share-with-patients.aspx). Our advisory group including members of the public were involved in discussing and reviewing draft information sheets.

### Sample size

The KSS arm will be limited to a maximum of 62 practices as this arm involves time and effort of clinicians during consultation. Sample size calculation has been computed based on the primary outcome of practice rate of antibiotic prescribing (per 1000 patients). In CPRD, the mean practice list size was 7981 and the overall rate of the number of antibiotic prescriptions (for any indication) was 598 per 1000 patients per year (SD 155). Assuming a reduction of 10% in the low-intensity KSS arm, its antibiotic prescribing rate will be around 538 per 1000 patients per year. Assuming an unchanged SD of 155 and practice attrition rate of 5%, randomising 62 practices to each of the two arms will provide 90% power to detect a 10% (54 per 1000 patients per year) between-arm difference in the overall rate of antibiotic prescribing (two-sided α=0.05), assuming a correlation of 0.82 between baseline and outcome antibiotic prescribing rate and analysing using analysis of covariance with baseline prescribing rate as covariate and 5% drop-out rate. For 80% power, 47 practices are needed in each arm. Sample size calculations were performed in PASS 2019 software. Our primary target is 112 practices although we will recruit up to 124 practices, given the limitation on numbers in the KSS arm. However, determination of the total sample size of practices will depend on practice consent to take part in the KSS evaluation and passing an assessment of IT system capability for the KSS installation.

### Study outcomes

The unit of analysis will be general practice. The primary clinical outcome will be the overall rate of antibiotic prescribing. One secondary outcome, relating to safety, will be infection-related complications as recorded in the primary care record, including pneumonia and lower respiratory tract infections, peritonsillar abscess, mastoiditis, intracranial abscess, empyema, scarlet fever, pyelonephritis, septic arthritis, osteomyelitis, meningitis, toxic shock syndrome and septicaemia, and Lemierre syndrome (as defined by Gulliford *et al*^15^). BRIT found that clinician-recorded infection-related complications provided comparable results as those recorded in linked hospital admission data.^16^ Another safety outcome will be hospital admissions for infection-related complications (linked hospital data are likely to be available within the shared care-record systems). The primary and safety-related secondary outcomes are equivalent to those used in a recent trial in UK primary care of a decision support system plus patient information sheets.^17^ Another secondary outcome will be the level of risk-based prescribing (ie, the proportion of antibiotic prescribing in patients with different risks) as based on the risk prediction scores as developed and validated in the BRIT project.^16^

A Statistical Analysis Plan (SAP), to be approved by the Steering Committee, will detail the planned analyses. Data analysts will have access to anonymised data from participating practices within a secure data analytic environment. Rates will be analysed using appropriate models with Poisson or normal error structures, weighted by practice size, and with adjustment for practice-level covariates including region (Greater Manchester, Wirral and Merseyside/Cheshire), study quarter, period of randomisation and baseline antibiotic prescribing, socioeconomic status, case-mix of patients and ethnicity distribution in each practice (including Charlson comorbidity score^18^), consultation rates for common infections, coding propensity and characteristics of patients with common infections. The coding propensity will be the proportion of antibiotic prescriptions with recent clinical record for common infection. The characteristics of patients with common infections will include the averages in each practice for mean age, sex, and predictors for infection-related complication (including clinical and medication risk factors^16^). Body mass index and smoking history will also be considered as potential predictors for infection-related complications; these will be discussed with the Study Steering Committee and will each be included in either the primary analysis, a sensitivity analysis or not included in the analysis. The primary analysis will be a complete case analysis (ie, excluding practices who drop out of the trial), unless attrition is higher than expected (ie, >10% overall or differential between-arm attrition of >10%).

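### The primary analysis excludes randomised practices that drop out, although their outcome may still be available from the shared care record

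*Protocol article*

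**What the plan says.** The Study outcomes section of the protocol article fixes the analysis set: "The primary analysis will be a complete case analysis (ie, excluding practices who drop out of the trial), unless attrition is higher than expected". It then defines higher than expected as "ie, >10% overall or differential between-arm attrition of >10" per cent. The document does not mention intention-to-treat and does not define dropping out.

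On the source of the outcome, the abstract states that "The data from practices participating in the trial and the dashboard infrastructure will be held within regional shared care record systems". The Study design section describes the sites as "general practices located in the North-West of England that provide patient-level data to a regional shared care record system". The Study outcomes section adds that analysts will see anonymised data from practices taking part. It does not say whether that access continues once a practice leaves.

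The Sample size section plans for 5% attrition. It caps the KSS arm "as this arm involves time and effort of clinicians during consultation".

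**The concern.** The protocol itself settles this rule; it is not a detail left to the statistical analysis plan. It takes randomised clusters out of the primary comparison after allocation.

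Two features make that questionable here. First, the primary outcome is a practice prescribing rate drawn from a routine data feed. That feed does not depend on whether anyone opens the KSS or a dashboard. A practice that stops taking part may therefore still have a usable outcome, in which case excluding it creates missing data that need not exist. Second, the burden on clinicians during consultations falls on the KSS arm only, which is a plausible reason for dropout to differ by arm.

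If practices that leave would have prescribed differently from those that stay, beyond what baseline prescribing predicts, the retained KSS practices no longer represent the arm as randomised. The between-arm difference is then biased.

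**Working it through.** **Inputs** (Sample size section unless stated): SD 155 per 1000 per year; baseline-outcome correlation 0.82 with analysis of covariance; target difference 54 per 1000; two-sided alpha 0.05; attrition 5%; 62 practices per arm for 90% power and 47 for 80%; primary target of 112 practices. The exception thresholds come from Study outcomes.

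**Residual SD.** 155 × √(1 − 0.82²) = 155 × √0.3276 = 88.7.

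**Reproducing the plan's sample size.** For a two-group comparison on this residual SD (noncentral t, df = 2n − 3), a difference of 54 needs 58 evaluable practices per arm for 90% power and 44 for 80%. Allowing for 5% attrition, 58/0.95 = 61.1, rounded up to 62, and 44/0.95 = 46.3, rounded up to 47. Both match the plan, so 88.7 and 54 are the right yardsticks.

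**How much loss the exception tolerates at 62 per arm.**
- Six KSS, no control: 6/124 = 4.8% overall, 6/62 = 9.7% differential. Complete case stays.
- Nine KSS, three control: 12/124 = 9.7% overall, (9 − 3)/62 = 9.7% differential. Complete case stays.

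**Bias.** Suppose k of the n KSS practices drop out and prescribe on average m residual SDs above the completers. The full-arm mean then exceeds the completers' mean by

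bias = (k/n) × m × 88.7.

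Control dropout is taken as uninformative and practices are weighted equally. The documents do not give m, so a range is shown.

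| Dropouts, KSS vs control (per arm) | m = 0.25 | m = 0.5 | m = 1.0 |
|---|---|---|---|
| 3 vs 3 (62), close to the planned 5% | 1.1 (2% of 54) | 2.1 (4%) | 4.3 (8%) |
| 6 vs 0 (62) | 2.1 (4%) | 4.3 (8%) | 8.6 (16%) |
| 9 vs 3 (62) | 3.2 (6%) | 6.4 (12%) | 12.9 (24%) |

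Example: (6/62) × 1.0 × 88.7 = 8.6, and 8.6/54 = 16%.

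The picture is similar at the primary target of 112 practices, 56 per arm. Five KSS dropouts and no control dropouts give 5/112 = 4.5% overall and 5/56 = 8.9% differential, still within both limits. At m = 1 the bias is (5/56) × 88.7 = 7.9, or 15% of 54.

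**Effect on the test.** For 6 vs 0, SE = 88.7 × √(1/56 + 1/62) = 16.4. The bias of 2.1 to 8.6 raises the two-sided type I error from 5% to between 5.2% and 8.2%. For 9 vs 3 (SE 16.8) it becomes 5.4% to 12.0%.

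**Price of analysing everyone.** With all 62 per arm and the full effect of 54, power is 92.0%. If six KSS dropouts are kept and have no effect at all, the average effect is 54 × (1 − 6/62) = 48.8 and power is 85.9%.

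**The case against.** **Data may not be available after dropout.** The abstract and Study outcomes both speak of data from practices taking part, and the Consent section requires the practice's agreement. If dropping out means withdrawing that agreement or leaving the shared record, the outcome may really be missing. This stands: the protocol makes continued availability likely but does not confirm it.

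**The protocol already has a safeguard.** Two numerical limits are set in advance, and one is aimed at differential loss. The analysis that would replace complete case may be named in the statistical analysis plan, so its absence here is no fault. The limits do give partial protection, but they count departures and say nothing about which practices leave. The working shows that they leave room for bias.

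**The size is assumed.** The upper figures need loss concentrated in the KSS arm and a gap of a full residual SD after baseline adjustment. At planned attrition the bias is modest. This also stands.

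Some stronger readings are tempting but not supported:

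- *Practices that do not use the KSS are excluded.* The rule concerns dropping out of the trial. The Consent section leaves use to the clinician, so low use is compatible with remaining in.
- *The comparison is as-treated.* Research questions says "Practices that have implemented the KSS will be compared with practices that have not", but the same sentence identifies this as a randomised cluster trial and Study design defines the arms by 1:1 randomisation. The wording is loose and does not set a different contrast.
- *KSS practices will be lost after randomisation because they cannot install the software.* The article notes that "The KSS has been developed for use with EMIS which is the most common primary care record system in England" and makes the total number of practices depend on "passing an assessment of IT system capability for the KSS installation". That reads naturally as screening before entry, and Technical description of the KSS links the choice of EMIS to the pool of practices that can be randomised.
- *The bias favours the KSS.* Nothing in the documents says whether practices that leave would prescribe more or less than predicted. If they would prescribe less, a bias of the same size runs against the KSS.

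**Conclusion.** The concern holds as a stated rule that removes randomised practices from the primary analysis when their outcomes may still be obtainable. The 10% limits allow a bias of about 2 to 9 per 1000 (4% to 16% of the 54 target) for six KSS dropouts against none, and about 1 to 4 per 1000 at planned attrition. These figures rest on an assumed gap of 0.25 to 1 residual SD between dropouts and completers, with uninformative control dropout. They show what is possible, not what is expected, and the direction is unknown. This should be fixed because the remedy is cheap and protects the randomised comparison. It does not show that the trial's result would be seriously wrong.

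**What to change.** Define dropping out, separating a practice that stops using the KSS or dashboards from one whose data can no longer be used. Make the primary analysis include all randomised practices in their allocated arm, using shared care record data after a practice stops taking part wherever data permission and the feed remain. Treat a practice as missing only if its data are unavailable. Keep the complete-case analysis as a sensitivity analysis.

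The cost is a change of wording in the protocol and analysis plan, and confirmation that data permission continues after a practice withdraws from the intervention. There is also some dilution of the effect if non-users are retained. No larger sample is needed.
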